## Abstract

**Background:**

Currently, the key advocacy in neuroscientific studies for stroke rehabilitation is that therapy should be directed towards task specificity performed with multiple repetitions. Circuit Class Therapy (CCT) is well suited to accomplish multiple task-specific activities. However, while repetitive task practice is achievable with circuit class therapy, in stroke survivors repetitive activities may be affected by poor neurologic inputs to motor units, resulting in decreases in discharging rates which consequently may reduce the efficiency of muscular contraction. To accomplish multiple repetitions, stroke survivors may require augmented duration of practice. To date, no study has examined the effect of augmented duration of CCT in stroke rehabilitation, and specifically what duration of CCT is more effective in influencing functional capacity among stroke survivors.

**Methods/design:**

Using a randomised controlled trial with blinded outcome assessment, this study is aimed at determining the effectiveness of structured augmented CCT in stroke rehabilitation. Sixty-eight stroke survivors (to be recruited from a tertiary health institution in Kano, Northwest, Nigeria) will be randomised into one of four groups: three intervention groups of differing CCT durations namely: 60 min, 90 min, and 120minuntes respectively, and a control group. Participants will take part in an 8-week structured intensive CCT intervention. Participants will be assessed at baseline, post-intervention, and six-month follow-up for the effectiveness of the varied durations of therapy, using standardised tools. Based on the WHO-ICF model, the outcomes are body structure/function, activity limitation, and participation restriction measures.

**Discussion:**

It is expected that the outcome of this study will clarify whether increasing CCT duration leads to better recovery of motor function in stroke survivors.

## Background

Stroke is a growing global health-care crisis, with grave and disabling consequences [1]. In most countries, stroke is the second or third most common cause of death, and one of the main causes of acquired adult disability [1, 2]. Motor impairments (of upper and lower extremities) are the major recognisable impairments caused by stroke, which are associated with limitations or decline in independent mobility [3–6].

Substantial evidence suggests that task-specific training can assist functional recovery in stroke rehabilitation, with the goal of achieving true recovery of function based on motor learning principles, including purposefulness, multiple repetitions, and intensified activity [7, 8]. Circuit Class Therapy (CCT) is a form of Task Specific Training (TST) that involves the practice of structuring tasks in a circuit or series of workstations. It satisfies the three key characteristics of an effective and efficient skill training programme [9] including: (i) using different workstations that allow people to practice intensively in a meaningful and progressive way to suit their respective needs; (ii) efficient utilisation of therapists’/trainees’ time; and (iii) it encompasses group dynamics such as peer support and social support [9, 11]. Several research trials have shown that CCT is effective in improving balance, transfers, gait, gait-related activities (such as climbing stairs) and upper limb functions in stroke survivors [12, 13], especially when applied within the first six months after stroke [12, 14–16] and even later [10, 13, 17–20].

The goal of CCT in stroke rehabilitation is to institute an enduring motor learning in order to optimise motor and functional recovery necessary for the achievement of community reintegration of stroke survivors. To accomplish sustained motor learning, rehabilitation must be geared towards a relatively permanent behavioural change, which is currently believed to manifest as a result of neuroplastic change in the brain itself [21]. Compelling evidence from neuroscientific studies suggest that neuroplastic changes in the cerebral cortex and in other parts of the central nervous system (CNS) are the physiological mechanism for effective motor skill retraining following stroke [22–26]. These studies identified TST and intensity of multiple repetitions as critical nexuses to enhancing neural reorganisation and “rewiring” in the CNS. By implication the damaged brain will therefore benefit from repeated sensorimotor inputs (efferent-afferent feedback loops) in order to remodel effectively for the attainment of motor/functional recovery in stroke survivors. This signifies the need for rehabilitation professionals to focus on meaningful, repetitive, and intensive specific tasks during a rehabilitation session [27].

Stroke survivors demonstrate poor activity tolerance [28] and performance [29]. These may suggest the need for longer duration to tolerate and perform repetitive activities. The need to augment the duration of therapy in CCT for stroke survivors can be considered based on pathophysiologic and clinical domains. Pathophysiologically, the sequelae of an upper motor neuron lesion result in hemiparesis/hemiplegia, marred balance and coordination and decreased proprioceptive feedback [30]. These put together will negatively affect daily activities and exercise performance, leading to activity intolerance, increased energy cost of activity, and a decline in overall performance after stroke [27]. Cumulatively, these factors result in longer reaction time and longer time to accomplish tasks, thus suggesting the need to give adequate time for the performance of multiple repetitive tasks in stroke survivors, well beyond age and gender-matched individuals without history of stroke. Four systematic reviews and one Cochrane review have shown that augmentation of exercise therapy and/or time of exercise therapy results in significant small to moderate gains in ADL, walking ability and walking speed [31–34].

Clinically, in CCT, participants are exposed to multiple progressively structured tasks to be accomplished within a session, and considering the pathophysiological challenge of stroke survivors, they may need more time to perform multiple repetitions to enable neuroplastic changes. Rose et al. [35] have proposed that planning the contents of a session in advance with predetermined progression of tasks may allow more time for in-session practice.

In summary, pathophysiological and clinical factors may in isolation or collectively support the need to examine the effect of augmented therapy time in CCT. However, while there is a need to investigate the effect of augmenting the duration of therapy, it is equally imperative to determine how acceptable these CCT durations are among stroke survivors.

### Objective

The objective of this study is to investigate the relative effectiveness of augmented durations of CCT on the functional capacity of stroke survivors. Additionally, the study will investigate the effectiveness of augmented duration of CCT on upper and lower extremity functions (with respect to body structure/function, activity limitation and participation restriction) post-stroke and the acceptability of the various CCT durations among stroke survivors. For these to be achieved outcomes of interest will be assessed based on the World Health Organisation International Classification of Function, Disability and Health model (WHO-ICF) [36].

## Methods/Design

### Study design/setting

This study is a randomised controlled trial of the effectiveness of augmented durations of a structured CCT model in the rehabilitation of stroke survivors. All participants will be recruited from Aminu Kano Teaching Hospital (AKTH) in Kano State, Northwest of Nigeria. The hospital (AKTH) is a tertiary health institution, situated in Kano, the most populous state in Nigeria, with over 9 million inhabitants [37]. It is a 500-bed-capacity hospital that receives patients from within Kano and the neighbouring states of Jigawa, Katsina, Kaduna, Bauchi and Zamfara states. The patronage list comprises primarily the indigenous Hausa Fulani tribe, although Nigerians of other tribes such as the Ibo and Yoruba ethnic groups also constitute a sizeable number of the clientele.

### Participants

Participants will include all stroke survivors in AKTH referred for physiotherapy by consulting physicians. However, only participants who meet the inclusion criteria will be considered for randomisation into the study groups (involving intervention and control groups). Participants will be considered eligible if: stroke is ascertained to be due to cerebrovascular accident; leading to unilateral motor deficits [14]; they provide a written informed consent; they are adult stroke survivors of ≥18 years of age; onset of stroke is ≥30 days; they possess sufficient cognition to participate (having a score of ≥24 points on mini-mental state examination); they are willing to participate in an 8-week intensive CCT programme; have the ability to walk for 10 m unsupported (walking aid is allowed); and have a minimum active wrist extension (2/5 on manual muscle testing). Participants will be considered ineligible if they present with precluding medical comorbidity to exercise, and history of any major surgical procedure significant enough to interfere with performance (general or orthopaedic) in an exercise therapy intervention.

Stroke survivors who meet the eligibility criteria will be randomised into one of four arms of the study, including three intervention categories (60 min CCT, 90 min CCT and 120 min CCT) and one control (60 min standard physiotherapy).

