### Sample size and power calculation

Using power calculations to detect a between-group difference of 42.5 m (0.43 effect size) for a 4-group repeated measure MANOVA in walking distance with 90 % power at α = 0.05, a total sample size of 56 was generated, using an estimated standard deviation (SD) for the calculation as adopted from a meta-analysis [9]. The 42.3 m was proposed as the minimum clinically important difference in walking distance, based on previous studies of implicit measurement error following repeated measurement of speed. The generated total sample size of 56, by implication, will give 14 participants as samples for each group. To incorporate drop-out to follow-up, we hope to recruit a total of 68 participants (17 participants per group). The power calculation was conducted using G*Power version 3.0.10.

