### Randomisation and blinding

Randomisation will be conducted using a computer-generated random allocation sequence schedule held by a third party, who will randomly allocate recruited participants into the study group (Fig. 1. outline of the study flow diagram based on CONSORT [38]). To eliminate bias, the assessment of outcome will be performed by (experienced/trained) blinded assessors, who will be blinded to the nature/type of intervention as well as the intervention groups of the participants. Participants will also be instructed not to disclose their individual intervention groups to the assessors.

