### Procedures

This study has been approved by both the Senate Research Grants and Study Leave Committee University of the Western Cape (South Africa) (ethics number 13/9/33) and the Human Research Ethics Committee of Aminu Kano Teaching Hospital (Nigeria) (NHREC/21/082008/AKTH/EC/1232).

Assessment of participants will be conducted at three stages (baseline, post-intervention, and at 6-months follow-up). To ensure a comprehensive assessment, we chose a battery of measures covering the WHO-ICF model [36]. We selected certain tools to cover the three key domains proposed by the ICF: body structures and function, activity and participation. At baseline, participants will be assessed for socio-demographic characteristics which will include personal demographic information and stroke-specific information. The personal demographic information will include age, sex, height, weight, marital status (pre- and post-stroke), educational qualification, employment (pre- and post-stroke), and tribe. The stroke-specific information will include time since stroke, type of stroke, hemispheric side of lesion, and use of cane. This will be followed by ICF-based assessments, all at baseline. The outcome measures to be employed for these assessments and their function/application are presented in Table 1.

**Table 1 Tab1:** Study assessment tools

Scales	Function/application
Body structure and function assessment	
i. Modified Tardieu Scale (MTS)	
	The MTS measures spasticity [39]. Descriptively, the MTS has two measurements, the quality of muscle reaction (ordinal scale) and the angle of reaction or angle of catch (ratio). The quality of muscle is scored from 0–5; 0 implies no resistance to Passive Range of Movement (PROM) and 5 indicating joint immobile. On the other hand Angle of catch can be understood via two factors of PROM, the speed of movement and joint angle. The reporting of MTS summarily, involve the quality of muscle and angle of reaction components making it to fit into the body structure and function of the ICF absolutely. It has excellent test retest reliability (ICC = 0.86) in stroke patient [40], with good convergent validity for both elbow and ankle joints (*r* = 0.86 and *r* = 0.62 respectively) [39].
ii. Medical Research Council Manual Muscle Testing (MMT)	

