### Data analysis

Data will be recorded in Microsoft Excel before being exported to Statistical Package for Social Science (SPSS). Both descriptive and inferential statistics will be used to examine the outcomes of the study.

Descriptive statistics of frequencies, percentages, mean, and standard deviation will all be used to describe baseline assessments and demographic characteristics of participants. Where appropriate, they will also be used at post-intervention and follow-up to describe relevant findings.

Between-groups relative mean differences of the dependent variables, (spasticity, muscle strength, functional independence, ADL, functional capacity, gait speed, upper extremity function and impairment) will be determined using the general linear model repeated measures, MANCOVA models (for each study domain, adjusted central on baseline as covariates). If the MANCOVA is found to be significant (Roy’s largest root), univariate between-groups results will be reported and pair-wise post hoc analysis will be performed using least significant difference.

A multiple regression analysis will be performed to investigate the relation between improvement at different time periods of CCT and performance in each of the specific dependent variables, to detect which of the durations most effectively predicts improvement in such a variable.

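### Time since stroke is recorded and has no upper limit at entry, but is not named as a covariate; prespecifying it is a nearly free and modest gain in precision

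*Protocol article*

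**What the plan says.** - **Eligibility** (Protocol article, Participants): "onset of stroke is ≥30 days". No upper limit is given.
- **Background**: circuit class therapy is described as effective "especially when applied within the first six months after stroke", and the same sentence adds that it also works later.
- **Baseline data** (Procedures): "The stroke-specific information will include time since stroke, type of stroke, hemispheric side of lesion, and use of cane".
- **Allocation** (Randomisation and blinding): a "computer-generated random allocation sequence schedule held by a third party". No stratification factor is described.
- **Models** (Data analysis): one repeated-measures MANCOVA per study domain, "adjusted central on baseline as covariates", followed by univariate results and pairwise comparisons. Time since stroke is not mentioned there.
- **Sample size**: a "between-group difference of 42.5 m (0.43 effect size") "for a 4-group repeated measure MANOVA in walking distance", giving 56 in total (14 per group), raised to 68 (17 per group) for drop-out.

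**The concern.** A participant at five weeks and one at five years after stroke can enter with the same walking distance and still be on different recovery paths. If so, the baseline score does not carry all of the prognostic information in time since stroke, and the rest stays in the error term. The article does more than leave covariates unmentioned: it states a covariate set, and that set omits a variable the trial already collects and its own background regards as relevant. With 14 to 17 per arm, two arms can differ noticeably in the share of early participants by chance. What is at stake is some precision, and the credibility of the one realised comparison if such an imbalance appears. Deciding to adjust only after seeing an imbalance would be a post hoc choice.

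**Working it through.** **Inputs from the protocol.** Four groups; three assessments; effect size 0.43; difference 42.5 m; α = 0.05; power 90 %; N = 56 (14 per group), recruiting 68 (17 per group).

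**Assumed, not in the documents.** Correlation between assessments ρ = 0.5. Partial R² of time since stroke, given arm and baseline score: 0 to 0.20.

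**1. Reproduce the planned total.** Repeated-measures F test for the between-group factor, reading 0.43 as Cohen's f, with m = 3 assessments:

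λ = N f² m / (1 + (m − 1)ρ) = 56 × 0.1849 × 3 / 2 = 15.53, with 3 and 52 degrees of freedom.

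Power is 0.905, and 56 is the smallest N reaching 0.90. The planned figure reproduces.

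**2. Add the covariate.** Divide λ by (1 − partial R²) and remove one error degree of freedom (52 to 51). This treats partial R² as the share of the error variance in that test.

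| Partial R² | λ | Power at N = 56 | Total N for 90 % |
|---|---|---|---|
| not in model | 15.53 | 0.9050 | 56 |
| 0 | 15.53 | 0.9045 | 56 |
| 0.05 | 16.35 | 0.9195 | 53 |
| 0.10 | 17.26 | 0.9337 | 51 |
| 0.20 | 19.41 | 0.9587 | 46 |

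The worst case is a loss of 0.05 percentage points; the best in this range is a gain of 5.4 points.

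**3. Is there bias?** For each partial R², 20,000 trials with no treatment effect were simulated (four arms of 14). ANCOVA on baseline alone was compared with ANCOVA on baseline plus time since stroke.

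| Partial R² | Mean error, baseline only (SD units) | Type I error, baseline only | Ratio of SEs, adjusted to baseline only |
|---|---|---|---|
| 0 | −0.003 | 0.049 | 1.01 |
| 0.05 | −0.002 | 0.048 | 0.99 |
| 0.10 | 0.004 | 0.049 | 0.96 |
| 0.20 | 0.005 | 0.047 | 0.90 |

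Simulation error of the mean is about 0.003. There is no bias and no inflation; only the standard error changes.

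**4. How far could chance imbalance move one estimate?** For two arms of 17, the standardised imbalance has SD √(2/17) = 0.343. At partial R² 0.10, the 95 % range of the resulting shift is 1.96 × 0.343 × √0.10 = ±0.21 SD. If 0.43 is instead a standardised mean difference, the implied SD is 42.5 / 0.43 = 98.8 m, and the shift is up to about ±21 m (±15 m at 0.05, ±30 m at 0.20). These are generous values, because the residual SD after baseline adjustment would be below 98.8 m.

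On the same scale, the whole 95 % sampling range of an arm contrast is 1.96 × 0.343 × 98.8 = ±66 m. Since (21/66)² ≈ 0.10, the 21 m is the tenth of the variance that was assumed. It is already inside the standard error, not added to it.

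**5. Imbalance as a share.** Assume 40 % of participants are early. With 17 per arm, a given pair of arms differs by at least 20 percentage points in 22 % of allocations, and by at least 25 points in 11 %. Some pair among the six differs by at least 25 points in 39 %. If early participants gained 50 m more (assumed), a 25-point imbalance would shift that pair by 0.25 × 50 = 12.5 m. This is 0.37 of the unadjusted standard error of 98.8 × 0.343 = 33.9 m.

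**The case against.** The strongest reply is that nothing here is wrong. A baseline-adjusted model on randomised arms is valid, broad eligibility is a design choice, and an article may leave further covariates and stratification factors to a fuller plan. The list in Data analysis is not said to be exhaustive. The baseline score may already absorb much of the effect of time since stroke, in which case the gain is close to nil. All of this stands, and it is why the point is an improvement and not an error. It does not remove the point, because the article does state a covariate set and a better one is available from data already collected.

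Three stronger readings are tempting and are not supported:

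- **That the arm differences would be biased.** A reader might infer this from the mix of early and late participants. Allocation is random, so imbalance averages to zero and is counted in the standard error (step 3).
- **That the 39 % describes the comparison of interest.** It is the chance for the worst of six pairs. For a given pair the figure is 11 %, and the metre shift rests on an assumed early share and an assumed extra gain.
- **That the background establishes faster recovery from the same baseline score.** The sentence concerns response to circuit class therapy and also supports later treatment. It justifies treating time since stroke as relevant, not any particular size. A main-effect covariate addresses prognosis; it would not capture a treatment effect that differs by time since stroke.

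**Conclusion.** The point holds as a nearly free improvement: low severity, moderate confidence. Time since stroke is open-ended at entry, recorded, and regarded by the protocol as relevant, but it is not named in the models. The consequence is lost precision and exposure to chance imbalance. Adjustment would reduce these but not remove them. Power at N = 56 would go from 0.905 to between 0.904 and 0.959, and the simulated standard error would change by between +1 % and −10 %, over an assumed partial R² of 0 to 0.20. The documents give no value for that quantity.

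The power figures also depend on reading 0.43 as Cohen's f with ρ = 0.5, while the metre figures depend on reading it as a standardised mean difference. The two readings are not interchangeable. Under the second, pairwise power is only about 0.21 with 14 per arm and 0.24 with 17. That is a separate matter, which a covariate of this size would not repair.

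**What to change.** In Data analysis, prespecify time since stroke at randomisation as one fixed covariate, alongside the baseline scores, in every between-arm model: the domain MANCOVAs, their univariate follow-ups and pairwise contrasts, and the regression on duration. Fix its form in advance. Log days is a sensible default, because eligibility without an upper limit can give a skewed distribution; under versus over six months is a simpler alternative.

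The cost is one error degree of freedom per outcome (52 to 51 at N = 56), with no new data and no change to eligibility or sample size.

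Optionally, if recruitment has not started, stratify the computer-generated sequence on under versus over six months. This is one extra factor in the allocation schedule, and the covariate should be kept in the models either way.

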### Sample size and power calculation

Using power calculations to detect a between-group difference of 42.5 m (0.43 effect size) for a 4-group repeated measure MANOVA in walking distance with 90 % power at α = 0.05, a total sample size of 56 was generated, using an estimated standard deviation (SD) for the calculation as adopted from a meta-analysis [9]. The 42.3 m was proposed as the minimum clinically important difference in walking distance, based on previous studies of implicit measurement error following repeated measurement of speed. The generated total sample size of 56, by implication, will give 14 participants as samples for each group. To incorporate drop-out to follow-up, we hope to recruit a total of 68 participants (17 participants per group). The power calculation was conducted using G*Power version 3.0.10.

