	MMT will be used to assess muscle strength for upper and lower extremities, attention will be paid to specific joints of both extremities. For the upper extremity attention will be focused on shoulder, elbow and wrist joints and for the lower extremity joints hip, knee and ankle will be measured. MMT is the best known and most frequently employed muscle strength grading system for manual muscle testing (MMT) [41]. It has a score range of 0–5, with 0 being the minimum and 5/5 the maximum. An excellent test-retest reliability for both right and left hip joints (ICC = 0.98 and ICC = 0.97 respectively) with osteoarthritis [42]. Its convergent validity ranges between adequate to excellent in different body parts [43].
Activity assessment	
i. Modified Rankin Scale (MRS)	
	The MRS is a hierarchical scale of 0–6 points that indicate “global disability”. It is the most prevalent functional outcome measure for stroke research. Lower scores on the scale suggest more independence and higher scores signify increased dependency. Its test-retest reliability ranged between adequate to excellent (Kappa = 0.67-0.96) [44], with an excellent convergent validity [45].
ii. Modified Barthel Index (MBI)	
	The MBI assesses ten functional tasks of daily living (activities of daily living – ADL). It scores the individual based on independence in each task. Scores range from 0 and 100, with a higher score indicating greater independence. The inter-rater reliability is sufficient at the item level (kappa 0.50–0.78) and good for the overall inter-rater agreement (intraclass correlation coefficient [ICC] 0.77) [46, 47].
iii. Six-minute Walk Test (6MWT)	
	6MWT is a clinically useful measure of walking ability post stroke, which incorporates the important requirements of ambulation, such as walking speed, dynamic balance, and submaximal endurance. It is performed at the individually determined fastest speed possible during walking, making it ideal for stroke survivors [48]. It measures an individual’s ability to walk for a maximum distance (meters) within 6 min. This test exhibits excellent test-retest reliability (ICC = 0.973; 95 % CI = 0.925 to 0.988), a minimal detectable change of 54.1 m, and an acceptable concurrent validity (*r* = 0.52 to 0.89) [48].
iv. 10 Meter Walk Test (10MWT)	

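### The 90 % power for a 42.5 m difference does not follow from the stated inputs: 56 participants result when 0.43 is taken as Cohen's f, but 42.5 m with an SD reads as a standardised mean difference

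*Protocol article*

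**What the plan says.** All of this is in the Protocol article. Under Sample size and power calculation, the calculation is introduced with "Using power calculations to detect a between-group difference of 42.5 m (0.43 effect size) for a 4-group repeated measure MANOVA in walking distance", and the result is given as "with 90 % power at α = 0.05, a total sample size of 56 was generated". The SD is attributed to a meta-analysis but its value is not printed. The total "will give 14 participants as samples for each group", and recruitment is raised to 68 (17 per group) to allow for drop-out. The software is G*Power 3.0.10.

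The next sentence gives the target slightly differently: "The 42.3 m was proposed as the minimum clinically important difference in walking distance".

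Under Procedures there are three assessments: baseline, post-intervention and six months. Table 1 in that section reports, for the six-minute walk test, an ICC of 0.973 (95 % CI 0.925 to 0.988) and "a minimal detectable change of 54.1 m".

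Under Data analysis, the outcomes are compared by repeated-measures MANCOVA with baseline as covariate. Pairwise least-significant-difference tests follow if that is significant.

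**The concern.** Two different indices can both be called an effect size here. For two groups, a mean difference over an SD is Cohen's d. A four-group F test uses Cohen's f, the SD of the group means over the within-group SD. For a given largest difference d among four groups, f is at most d/2. Entering a d of 0.43 where f is expected therefore at least doubles the effect that is being powered for.

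If that happened, the 90 % belongs to a difference two to nearly three times the one named as the minimum clinically important difference. The trial would be much less likely to detect 42.5 m than its only printed power statement says.

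**Working it through.** **Inputs.** From the article: 4 groups, 3 measurements, alpha 0.05, 90 % power, effect size 0.43, difference 42.5 m, N = 56. Assumed because not stated: correlation 0.5 among the repeated measurements.

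**1. Reproducing 56.** Repeated measures, between-groups F test: λ = f²·N·m / [1 + (m − 1)ρ], with df 3 and N − 4.
- f = 0.43, m = 3, ρ = 0.5, N = 56: λ = 0.1849 × 56 × 3 / 2 = 15.53, power 0.905.
- N = 55: power 0.899. So 56 is the smallest N that reaches 90 %.
- The match depends on ρ: the formula gives 51 at ρ = 0.4, 61 at 0.6 and 66 at 0.7.
- A group-by-time MANOVA gives 52 to 56 under two of three noncentrality conventions, again with 0.43 on the f scale.
- With 0.43 as d in a two-group comparison, 90 % power needs 114 per arm. No route that was tried gives 56 with 0.43 as d.

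**2. Reading 0.43 as difference over SD.** SD = 42.5 / 0.43 = 98.8 m. The value of f depends on the pattern of the four means (same test, ρ = 0.5):

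| Pattern of means | f | Power, N = 56 | Power, N = 68 | N for 90 % (equal arms) |
|---|---|---|---|---|
| Two extremes, two midway: d·√(1/8) | 0.152 | 0.18 | 0.21 | 416 |
| Equally spaced: (d/2)·√(5/9) | 0.160 | 0.19 | 0.23 | 372 |
| One against three: d·√3/4 | 0.186 | 0.25 | 0.30 | 280 |
| Two against two: d/2 | 0.215 | 0.33 | 0.39 | 212 |

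Conversely, f = 0.43 means a largest difference of 0.86 SD (two against two) to 1.22 SD (two extremes). At SD 98.8 m that is 85 to 120 m.

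**3. Reading 0.43 as f.** A 42.5 m largest difference then needs an SD of 42.5 / 1.22 = 35 m to 42.5 / 0.86 = 49 m. Table 1 allows a check, if its figure is a 95 % minimal detectable change:
- Standard error of measurement = 54.1 / (1.96 × √2) = 19.5 m.
- Cross-sectional SD = 19.5 / √(1 − 0.973) = 119 m.
- Over the ICC interval of 0.925 to 0.988: 71 to 178 m.

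The value 98.8 m lies inside this range; 35 to 49 m lies well below it.

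**4. With baseline adjustment.** I assume that the two post-baseline values are averaged, baseline is the covariate, and all three visits share a correlation ρ. Then λ = f²·N / [(1 + ρ)/2 − ρ²], with df 3 and 51 at N = 56. At SD 98.8 m, over the patterns of means:

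| ρ | Omnibus power |
|---|---|
| 0.5 | 0.22 to 0.42 |
| 0.7 | 0.30 to 0.57 |
| 0.8 | 0.41 to 0.72 |
| 0.9 | 0.69 to 0.95 |
| 0.95 | 0.94 to above 0.99 |

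At ρ = 0.9 only the two-against-two pattern exceeds 90 %.

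**5. One pairwise contrast of 42.5 m.** Two-sample t test with d = 0.43, unadjusted: power about 0.20 at 14 per arm and 0.23 at 17 per arm.

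**The case against.** The article never says whether 0.43 is d or f, and it gives no SD, correlation or tested term. A reader might infer that entering d as f is proven. It is not: the exact match at 56 rests on an assumed correlation of 0.5. What remains is that every route found to 56 uses the f scale, while the sentence ties 0.43 to a difference in metres and an SD.

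A reader might also infer that Table 1 rules out an SD of 35 to 49 m. It does so only for a cross-sectional SD. An SD of change could be that small. From a cross-sectional SD of 119 m this needs a correlation with baseline of about 0.91 to 0.96, since SD of change = SD × √(2(1 − ρ)). From 71 m it needs about 0.76 to 0.88. The article states no such SD type or correlation, but the possibility stands.

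The 18 to 33 % comes from a test that averages in the baseline visit and ignores the planned covariate. That is fair criticism of those figures as a forecast. They show what the formula behind 56 yields once the index is converted, and step 4 gives the adjusted range. A group-by-time test does not rescue the claim either. Entering f = 0.215 directly at ρ = 0.5 gives 0.83. A difference present only at the two post-baseline visits, however, has an interaction f of at most 0.10, with power of about 0.13 to 0.22.

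Finally, a reader might take the trial to claim that it can exclude an effect of duration. The article speaks only of detecting one. Nor is it an error that the power refers to an omnibus test, because the article says so openly.

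**Conclusion.** The point holds as an inconsistency in the power statement. The inputs as printed do not give 90 % power for 42.5 m with 56 participants. If 0.43 is difference over SD, which is the natural reading, 56 does not follow. If it is f, the SD must be a change or baseline-adjusted SD far below the cross-sectional value that Table 1 implies.

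The direction is well supported; the size is conditional. At SD 98.8 m, power at 56 participants runs from about 18 to 33 % in the reproduced test. With baseline adjustment it runs from about 22 % to 95 % over correlations of 0.5 to 0.9. Ninety per cent needs a correlation near 0.9 with the most favourable pattern of means, or about 0.95 otherwise. The mismatch between 42.5 and 42.3 m has no material effect on these figures.

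**What to change.** Keep recruitment at 68 and rewrite the paragraph:
- Give one target difference (42.5 or 42.3 m).
- State the SD and its type (cross-sectional, change or baseline-adjusted), the correlation, the assumed pattern of the four means, and the tested term.
- Convert the difference to f from these inputs.
- Replace the 90 % with the power achieved for the target. Alternatively, state the difference detectable at 90 %, which is 85 to 120 m at SD 98.8 m under the formula that reproduces 56.

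Optionally, report power for the pairwise contrasts and say that non-significant results will be interpreted through confidence intervals.

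The cost is one reworded paragraph and probably a less favourable power figure. No further participants are needed.
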